#### 5.1.2 Secondary outcomes

Assess 1) safety and tolerability; 2) secondary measurements of clinical efficacy and 3) explore putative mechanisms of action for the effect of MSC

1. MSC therapy will demonstrate safety and tolerability comparable to placebo in terms of serious adverse reactions and immunologic responses.

- New-onset organ failure defined as a significant acute change in the kidney or liver function, leukocytosis, leukopenia or anemia sustained over 3 months; > 75 % reduction in GFR compared to baseline; altered liver function as defined by ALT >150 U/L and or total bilirubin >1.6 mg/dl; or leukopenia defined as < 4K WBC count or anemia as defined by Hgb < 12 for men and < 11 for women.
  - Immunologic responses: Donor specific antibodies (DSA) in serum of patients will be measured and compared to baseline to determine if there is a development of antibody response to donor HLA. (Please refer to section 11.2)
2. MSC therapy will improve motor function, disability, quality of life, non-motor symptoms, cognition, and behavioral changes relative to placebo.
- Motor function: characterized by a change in MDS-UPDRS Total and Motor scores and Timed-Up-and-Go (TUG) from baseline. Immediate response will be assessed at weeks 29, 39, 52, and 78. Normal progression in UPDRS-T is defined by > 8-14 points per year Therefore abnormal clinical deterioration is an increase of >12 points per year in the “Off” state. For the UPDRS-M, the literature supports a natural progression of 3-6 points per year and this equivalent for the MDS-UPDRS motor section; therefore, abnormal clinical deterioration is an increase of > 6 points per year. TUG progression is defined as a +/- 3 seconds difference every 6 months.
  - Global measurement of disability as measured by the change in the screening “Off” modified Hoehn and Yahr (H&Y) at the final visit. Expected progression is defined as a < 1.0 increase in H&Y every 2 years. Therefore, clinically significant deterioration would be > 0.5 increase in the H&Y over 1-year.

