  - Quality of life: based on changes in the modified Schwab and England activities of daily living scale (ADL), Parkinson's Disease Questionnaire 39 (PDQ-39) and EuroQol- 5 Dimension (EQ-5D) from screening and at the final visit. The normal progression is an annual change of 10% in ADL and a change of less than 10% of the PDQ-39 at the final visit compared with the screening visit. Therefore a change of > 10% in ADL or the PDQ-39 over the 1 year study period will be considered clinically significant. For the EuroQol- 5 Dimension (EQ-5D), simulation-based estimates defined the minimally important difference (MID) index score to be between 0.037 and 0.069.
  - Non-motor symptoms: The non-motor symptoms questionnaire (NMS) and The University of Pennsylvania Smell Identification Test (UPSIT- 40 odor test booklet).
  - Cognitive function: measured by the change in Montreal Cognitive Assessment (MoCA) from screening to final visit. Normal change is less than 3 points per year. Therefore a  $\geq 3$  point change over a one year study will be considered clinically significant.
  - Behavioral changes: The Columbia Suicide Severity Rating Scale (C-SSRS), Geriatric Depression Scale-Short Form (GDS-SF), and Parkinson Anxiety Scale (PAS). Suicidal ideation will be assessed by the Columbia Suicide Severity Rating Scale (C-SSRS); any

positive response to any of the questions will be considered significant and would require further investigation. A score of 8 or more in the Geriatric Depression Scale will be considered significant and would require further investigation.

3. Explore putative mechanisms of action for the effect of MSC therapy. We will assess the putative paracrine mechanism of MSCs using neuroimaging and measuring concentrations of cytokines, chemokines, growth factors, neurotransmitters and alpha-synuclein oligomers in the blood (serum or plasma) and CSF.
  - Neuroimaging: 3 imaging time points per patient, baseline, week 40, and week 88.
    - Perfusion MRI: We will measure resting cerebral blood flow (CBF) using a pseudo-continuous arterial spin labeling (pCASL) MRI sequence with gradient-echo echo-planar imaging (EPI). Recent ASL studies of PD patients report wide-spread cortical hypoperfusion and, subcortically, hypoperfusion of the caudate nucleus.

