## 6.2 Exclusion criteria

- Atypical, vascular, or drug-induced Parkinsonism.

- An atypical DAT scan or MRI supporting an alternative explanation for PD symptoms.
- Presence of any red flags of atypical parkinsonism.
- Patient not on levodopa containing medications or dopamine agonist.
- Unwilling to undergo a Levodopa challenge.
- Clinical features of psychosis or refractory hallucinations.
- A Montreal Cognitive Assessment (MoCA) score of less than 25 (*See Appendix C for a copy of MoCA*).
- Uncontrolled seizure disorder, defined as a seizure within the last 6 months.
- Abnormal Kidney and liver function defined as GFR <45mL/min/m^2, or 2 times the normal range defined by the laboratory for ALT and AST..
- Presence of anemia defined as: Hgb <12g/dl for men and <11g/dl for women or Hct < 38% for men and < 34 % for women.
- Presence of clinically refractory orthostatic hypotension at the screening visit.
- Body mass index of ≥ 40. This cut off is based on the high likelihood of a traumatic LP at this BMI and/or failure to obtain an LP.
- Cardiac disease: History of congestive heart failure, clinically significant bradycardia, presence of 2nd, or 3rd-degree atrioventricular block.
- Pulmonary disease: COPD with oxygen-requirement at rest or with ambulation; or moderate to severe asthma.
- Active malignancy under treatment within 2 years prior to the screening visit, except for cancer in situ NXMX (TNM staging).
- Any current suicidal ideation or behaviors defined by 1 or more positive answers on the Columbia Suicide Severity Rating Scale (C-SSRS) in the last month.
- Active autoimmune disorder or immunocompromised state, including chemotherapy administration within the last three years or current immunosuppression as defined by WBC <3 x 10^3 cells/ml.
- History of medium or large size vessel cerebrovascular accidents.
- History of traumatic brain injury with loss of consciousness and residual neurologic symptoms.
- Major surgery within the previous 3 months or planned in the ensuing 6 months.
- Clinically significant abnormalities in the Screening visit laboratory studies.
- History of use of an investigational drug 4 months prior to the screening visit.
- Currently enroll in an interventional clinical trial.
- History of brain surgery for PD.
- History of stem cell treatment for any indication within 3 years prior to the screening visit.

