## 10. Study schedule

The study will last a total of one year and 8 months (88 weeks) per patient (3 groups) and will include 11 clinical visits and 10 telephone evaluations (*Please see section 10.3 for the study timeline and 10.4 for study schedule*).

There are 6 types of clinical visits: Screening, Baseline, Infusion, Safety and Clinical assessment, unscheduled visit, and final visit plus phone call evaluations starting after the first infusion.

- Visit #1 Screening Visit (between week -12 to week -3): after signing the consent and discussing the purpose and timeline of the study, the PI will confirm the PD diagnosis and establish the current disease stage. At this visit, the CRU staff will collect blood for laboratory assessment. The purpose of this visit is to ensure that the patient meets the inclusion and exclusion criteria.
- Visit #2 Baseline visit (between week -11 to week-1): the purpose of this visit to obtain baseline measurements on serum, plasma, CSF, and neuroimaging.
- Visit #3 Infusion Day (week 0): First IV MSCs infusion.
- Visit #4 Clinical and Safety assessment (week 9+/-1.5 week): the purpose of this visit is to determine the safety and the immediate immunological, physical and neurological response to the first infusion.
- Visit #5 Infusion Day (week 18+/-1 week): Second IV MSCs infusion.
- Visit #6 Clinical and Safety assessment (week 27+/-1.5 week): the purpose of this visit is to monitor safety and the immunological, physical and neurological response to the second infusion.
- Visit #7 Infusion Day (week 36+/-1 week): Third IV MSC infusion
- Visit #8 Clinical and Safety assessment (week 40+/-1.5 week): the purpose of this visit is to monitor the safety and the immunological, physical and neurological response to the third infusion. Additionally, to collect enough data for our first interim analysis.

- Visit #9 Clinical and Safety assessment (week 49+/-1.5 week): the purpose of this visit is to monitor the safety and the immunological, physical, and neurological response to the infusions.
- Visit #10: Clinical and Safety assessment (week 62+/-1.5 week): the purpose of this visit is to monitor the safety and the immunological, physical, and neurological response to the infusions.
- Visit # 11: Final visit (week 88+/-1.5 week): the purpose of this visit is to determine the physical and neurological response to the complete MSC treatment.

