|                     | MDS-UPDRS On                                                     | X                         |                            |                  |                           |                          |                            |                          |                               |                               |                            |                               |                            |                                   |
|                     | Questionnaires: ADL, PAS, GDS, PDQ-
39, C-SSRS, EQ-5D-5L, NMS | X                         |                            |                  | X                         |                          | X                          |                          | X                             |                               | X                          | X                             |                            | X                                 |
| Laboratory          | Lumbar puncture**                                                |                           | X                          |                  |                           |                          |                            |                          |                               | X                             |                            |                               |                            |                                   |
|                     | CBC with differential and CMP                                    | X                         |                            |                  | X                         |                          | X                          |                          | X                             |                               |                            | X                             |                            | X                                 |
|                     | Dipstick UA                                                      | X                         |                            |                  |                           |                          |                            |                          |                               |                               |                            | X                             |                            |                                   |

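### ADL and MoCA cut-offs set for one year are applied over 1.74 to 1.92 years, and the UPDRS total bands for normal and abnormal progression overlap

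*Protocol*

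**What the plan says.** Protocol section 5.1.2 gives, for most clinical scales, a norm for progression and a cut-off beyond which change counts as significant.

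- **ADL and PDQ-39**, screening to final visit: "Therefore a change of > 10% in ADL or the PDQ-39 over the 1 year study period will be considered clinically significant". The ADL norm is 10% a year. The PDQ-39 norm is under 10% at the final visit against screening.
- **MoCA**, screening to final visit: the norm is under 3 points a year, and 3 or more points over a one-year study is significant.
- **UPDRS total**: "Normal progression in UPDRS-T is defined by > 8-14 points per year". The next sentence calls a rise of more than 12 points a year abnormal.
- **UPDRS motor**: 3 to 6 points a year is natural, more than 6 abnormal.

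The duration is in section 10: "The study will last a total of one year and 8 months (88 weeks) per patient". The starting point is "Visit #1 Screening Visit (between week -12 to week -3").

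On laboratory safety, section 5.1.2 lists under new-onset organ failure "leukocytosis, leukopenia or anemia sustained over 3 months", with "leukopenia defined as < 4K WBC count". Section 6.2 excludes "current immunosuppression as defined by WBC" below 3 x 10^3, printed per ml. The row "CBC with differential and CMP" in the section 10.3 schedule table is marked at screening, weeks 9, 27, 40 and 88, and early termination.

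**The concern.** A limit equal to one year's normal change is tight but coherent at one year. Held fixed while the interval nearly doubles, it starts to capture patients who progress at the rate the same section calls normal. Placebo and active patients are judged by the same limit, so the likely effect is a higher count of significant changes in all three arms and a diluted contrast between them, with about 15 patients per arm.

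The UPDRS total bands leave part of the range with two labels, so two analysts could classify the same patient differently. For leukopenia, a patient may enter with a count that already meets the event level. For blood counts generally, the visit lists, the schedule table and the persistence rule do not describe the same set of tests.

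**Working it through.** **1. Study length.** 88 weeks / (365.25/7 = 52.18 weeks a year) = 1.69 years = 20.2 months. This reproduces the protocol's one year and 8 months.

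**2. Interval for ADL and MoCA.** From screening at week -3: 88 + 3 = 91 weeks, 91/52.18 = 1.74 years. From week -12: 88 + 12 = 100 weeks, 100/52.18 = 1.92 years. The 1.5-week window on the final visit widens this only to 1.72-1.95 years.

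**3. ADL.** Normal change over the interval is 10% x 1.74 = 17.4% to 10% x 1.92 = 19.2%, against a limit of more than 10%. Any steady rate above 10/1.92 = 5.2% to 10/1.74 = 5.7% a year passes the limit. How far this alters recorded classifications depends on how the percentage is read:

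- *Scale points, whole 10-point steps (section 8.5.4).* More than 10 means at least 20 points. Annualised, 20 points is 20/1.92 = 10.4 to 20/1.74 = 11.5 a year, still above 10, and one step is 5.2 to 5.7 a year, still below. The fixed and annualised limits pick the same patients.
- *Scale points, values between steps.* Appendix F asks for a number between 1 and 100. A 15-point fall passes the fixed limit, yet is 15/1.92 = 7.8 to 15/1.74 = 8.6 a year, within the norm.
- *Relative to screening.* One step from 80 is 10/80 = 12.5%, over the fixed limit, yet 12.5/1.92 = 6.5 to 12.5/1.74 = 7.2% a year, within the norm.

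**4. MoCA.** The steady rate that reaches 3 points is 3/1.92 = 1.57 a year at 100 weeks and 3/1.74 = 1.72 at 91 weeks. Rates from there up to just under 3 a year are normal by the protocol and significant by its limit. One year's norm scaled to the interval is 3 x 1.74 = 5.2 to 3 x 1.92 = 5.7 points. In whole points, changes of 3, 4 and 5 are flagged although 5 points is only 5/1.92 = 2.6 to 5/1.74 = 2.9 a year.

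**5. UPDRS total.** Normal runs to 14 a year and abnormal starts above 12. The overlap is 14 - 12 = 2 points of a band 14 - 8 = 6 points wide. Motor: 3 to 6 against more than 6, so no overlap. Both limits are already annual rates, so study length does not affect them.

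**6. PDQ-39.** Norm under 10% and limit above 10%, both at the final visit against screening. They agree; only the one-year label is wrong.

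**7. White cells.** Event below 4K; exclusion below 3K if per microlitre is meant. Counts from 3.0 to just under 4.0K may enter and already lie below the event limit. As printed, 3 x 10^3 per ml is 3 cells per microlitre. The haemoglobin event and entry limits match each other (12 for men, 11 for women).

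**8. Blood counts.** Gaps between post-infusion draws in the table: 27 - 9 = 18 weeks, 40 - 27 = 13 weeks (10 to 16 with windows), 88 - 40 = 48 weeks. Three months is 52.18/4 = 13 weeks. The rule can be checked up to week 40, only just for the second gap. After that no repeat is scheduled until week 88. The visit lists in 10.1.4 and 10.1.5 name no blood CBC or metabolic panel; the only CBC there is on CSF.

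**The case against.** The strongest reply is that nothing shows these cut-offs drive an analysis. Hypothesis 2.1 in section 14.3 models significant worsening without citing section 5.1.2, and section 16 has its own motor limits for board review. MoCA belongs with efficacy under Hypothesis 2.2, which estimates improvement as a function of treatment. This stands. A reader might infer that the safety analysis misclassifies patients; the documents support only a risk, clearest for ADL, which Hypothesis 2.1 names and for which section 5.1.2 alone defines a significant change.

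Second, the ADL steps blunt the effect. This also stands: on whole steps read in points, the fixed and annualised limits agree. It does not help MoCA. A MoCA at week 49, 52 to 61 weeks after screening, would give a near one-year comparison, but section 5.1.2 specifies the final visit.

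Third, the two white-cell limits serve different purposes, the event is headed new-onset, and section 6.2 also excludes clinically significant screening laboratory abnormalities. That largely answers the leukopenia point; the unit and the baseline rule still need stating.

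Fourth, a reader might infer that there are no confirmatory laboratory tests. The table repeats them at weeks 9, 27, 40 and 88, and section 10 allows unscheduled visits. It is also unclear whether the three-month rule covers the GFR, ALT and bilirubin limits, which follow a semicolon. The gap that remains is weeks 40 to 88, and an abnormality first seen at week 88.

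**Conclusion.** The point holds in limited form. The ADL and MoCA limits are worded for one year and applied over 1.74 to 1.92 years. For MoCA, changes of 3 to 5 points fall within the protocol's annual norm yet count as significant. For ADL, normal progression is 17 to 19% against a 10% limit, but whether any patient is reclassified depends on reading the percentage as relative to screening or on scores between steps being recorded. These figures assume steady change and the nominal visit weeks. UPDRS total rises above 12 and up to 14 a year carry two labels.

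A reader might extend the interval argument to PDQ-39, or the overlap to the motor score; neither follows, since both are internally consistent. The white-cell limits and the laboratory lists are matters to reconcile, not demonstrated errors in the results. No effect on the primary outcome is claimed.

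**What to change.** In section 5.1.2:

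- Divide ADL and MoCA change by each patient's elapsed years from screening before applying the per-year limit, and say whether the ADL percentage means scale points or change relative to screening.
- Replace the one-year wording with the actual interval. Leave the PDQ-39 limit as it is and correct only its label.
- Reconcile the UPDRS total bands so that no annual rise is both normal and abnormal.
- State that leukopenia is judged against the patient's baseline, as new-onset implies, and reconcile the event limit with the entry limit in section 6.2, including its unit.

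In section 10: reconcile the visit lists in 10.1.4 and 10.1.5 with the schedule table, say which organ-failure criteria the three-month rule covers, and say how it is applied to a finding at week 40 or week 88, given that no repeat is scheduled between those weeks.

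The cost is wording, with no change to sample size or visits. An added draw at week 62 is a preference and is not required here: it falls 62 - 40 = 22 weeks after week 40, so it would not be a three-month confirmation, and it would leave an abnormality first seen at week 88 unconfirmed.

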## 6. Study subjects

The target population includes the following characteristics: male or female sex; any ethnic, racial or socioeconomic background; sporadic late-onset PD; PD diagnosed by a neurologist; motor symptoms for 2-10 years and age between 50–79 years old at the start of the trial. Since the prevalence of PD in men is slightly higher than women at a 3:2 ratio, we anticipate that our

recruited population will have a similar gender distribution. A period of 2-10 years from motor symptom onset or disease diagnosis defines a mild to moderate disease stage and medically responsive phase of PD. Our research suggests that peripheral immune response in PD patients, which we hypothesize will be modified by MSC treatment, diminishes 6–10 years after the time of diagnosis. In order to participate, patients must be able to demonstrate  $\geq 33\%$  reduction of motor symptoms as determined by the motor subscale of the MDS-UPDRS in the levodopa OFF state vs. the levodopa ON state. The clinical diagnosis must be confirmed by a Movement Disorders Specialist and the PI at the screening. Patients with PD who meet the above criteria must be able to safely tolerate an OFF medicine state as defined by not taking levodopa therapy for 12 hours prior to testing.

Note: At any point during the trial patients will be allowed to receive a Covid-19 vaccine against SARS-CoV-2 approve by the FDA, however, to minimize a confounder effect, this should not be scheduled 8 days prior to an infusion visit or 13 days after an infusion visit.

## 6.1 Inclusion Criteria

- Men and women between the ages of 50 and 79 years.
- Diagnosis of Parkinson's disease by the UK brain bank criteria including the presence of 1 cardinal signs of PD plus bradykinesia. Diagnosis will be confirmed by the PI or other specialists in Movement Disorders and based on medical history, physical and neurological exams. Patients should have an asymmetric unilateral symptoms onset and supporting features (*See Appendix A for a copy of the UK brain bank criteria*).
- A modified Hoehn and Yahr stage of 3 or less in the levodopa OFF state. (*See Appendix B for a copy of the modified Hoehn and Yahr*)
- Date of Diagnosis of PD between 2 to 10 years, as documented in the medical record.
- Robust response to dopaminergic therapy (defined as greater than or equal to 33% reduction in symptoms (on the MDS-Unified Parkinson's Disease Rating Scale part III) when measured in the ON medicine state compared to OFF state).
- If the subject is taking any central nervous system acting medications (e.g., benzodiazepines, antidepressants, hypnotics, stimulants), the regimen must be optimized and stable for 60 days prior to the screening visit.
- A stable Parkinson's disease symptomatic medical regimen therapy for at least 60 days prior to infusion and not projected to require additional Parkinson's disease symptomatic therapy for at least three months after the last infusion.
- Women of childbearing potential will be required to use a reliable form of contraception from 60 days prior to baseline visit until 6 months after the final dose of the study drug.

## 6.2 Exclusion criteria

- Atypical, vascular, or drug-induced Parkinsonism.

- An atypical DAT scan or MRI supporting an alternative explanation for PD symptoms.
- Presence of any red flags of atypical parkinsonism.
- Patient not on levodopa containing medications or dopamine agonist.
- Unwilling to undergo a Levodopa challenge.
- Clinical features of psychosis or refractory hallucinations.
- A Montreal Cognitive Assessment (MoCA) score of less than 25 (*See Appendix C for a copy of MoCA*).
- Uncontrolled seizure disorder, defined as a seizure within the last 6 months.
- Abnormal Kidney and liver function defined as GFR <45mL/min/m^2, or 2 times the normal range defined by the laboratory for ALT and AST..
- Presence of anemia defined as: Hgb <12g/dl for men and <11g/dl for women or Hct < 38% for men and < 34 % for women.
- Presence of clinically refractory orthostatic hypotension at the screening visit.
- Body mass index of ≥ 40. This cut off is based on the high likelihood of a traumatic LP at this BMI and/or failure to obtain an LP.
- Cardiac disease: History of congestive heart failure, clinically significant bradycardia, presence of 2nd, or 3rd-degree atrioventricular block.
- Pulmonary disease: COPD with oxygen-requirement at rest or with ambulation; or moderate to severe asthma.
- Active malignancy under treatment within 2 years prior to the screening visit, except for cancer in situ NXMX (TNM staging).
- Any current suicidal ideation or behaviors defined by 1 or more positive answers on the Columbia Suicide Severity Rating Scale (C-SSRS) in the last month.
- Active autoimmune disorder or immunocompromised state, including chemotherapy administration within the last three years or current immunosuppression as defined by WBC <3 x 10^3 cells/ml.
- History of medium or large size vessel cerebrovascular accidents.
- History of traumatic brain injury with loss of consciousness and residual neurologic symptoms.
- Major surgery within the previous 3 months or planned in the ensuing 6 months.
- Clinically significant abnormalities in the Screening visit laboratory studies.
- History of use of an investigational drug 4 months prior to the screening visit.
- Currently enroll in an interventional clinical trial.
- History of brain surgery for PD.
- History of stem cell treatment for any indication within 3 years prior to the screening visit.
- Unable to return for follow-up visits for clinical evaluation, laboratory studies, or imaging evaluation.
- Unable to obtain peripheral IV access at the screening visit.
- Not willing to allow physical exam videotaping.
- Refusal or inability to undergo the lumbar puncture.

- Refusal or inability to undergo the MRI procedures.
- Substance abuse disorder.
- Active anticoagulation treatment and/or abnormal INR (with the exception of Aspirin).
- Any other condition that the investigator feels would pose a significant hazard to the patient if enrolled or complicate the study assessments.

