#### Medications or Supplements Not Allowed

The regular use of over the counter medications other than a standard daily multivitamin, pain medication, antihistamines, and cold medications or any experimental medication is not allowed.

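### Section 6.2 prints two eligibility limits in faulty units (WBC and GFR) and sets a one-month window for suicidal behaviour that conflicts with the trial's own C-SSRS form

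*Protocol*

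**What the plan says.** All three items are bullets in Protocol section 6.2.

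- **White cells.** The bullet starts with "Active autoimmune disorder or immunocompromised state, including chemotherapy administration within the last three years or current immunosuppression as defined by WBC", and its last limb in full is "current immunosuppression as defined by WBC <3 x 10 3 cells/ml". Section 5.1.2, in the safety outcomes, has "leukopenia defined as < 4K WBC count", with no volume unit.
- **Kidney function.** The limit is "GFR <45mL/min/m 2" (the final 2 is the exponent of m). The unit carries no 1.73. The only other GFR figure, in section 5.1.2, is a percentage fall from baseline, so it does not show which unit was meant.
- **Suicidality.** The bullet excludes "Any current suicidal ideation or behaviors defined by 1 or more positive answers" on the C-SSRS, with a one-month window covering ideation and behaviour alike. Sections 8.5.9 and 10.1.1 specify the Lifetime/Recent version at screening. On that form (Appendix I) the recent column covers 1 month for ideation and 3 months for behaviour.

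Section 6.2 also excludes clinically significant abnormalities in the screening laboratory results. Its last bullet lets the investigator exclude anyone for whom participation would be hazardous or would complicate the assessments.

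**The concern.** A numeric exclusion is meant to give the same answer whoever applies it. Each of these three, taken as printed, either cannot do its work or gives an answer that depends on the reader.

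The white-cell limit matters most. The product is allogeneic, the proposed mechanism is peripheral immune modulation, and leukopenia is a named safety outcome. The Phase I table in section 3.5 lists lymphocyte decreases in 3 + 2 + 0 + 1 = 6 of 20 patients, described as mild and transient. If the entry count excludes nobody, a patient can enter already below the outcome's own limit, and the numeric rule will not prevent it. The anaemia limits show the contrast: haemoglobin 12 for men and 11 for women appear both at entry and in the outcome.

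For GFR the stake is different: a literal reading could turn away patients whom the sponsor meant to enrol. For the C-SSRS, site staff may not be able to decide eligibility from the completed form.

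**Working it through.** The protocol derives no figure here, so there is nothing to reproduce. The check is unit conversion and a side-by-side reading.

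**1. White cells**

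Inputs: 3 x 10^3 cells/ml (section 6.2); 4K (section 5.1.2, volume unit not given, assumed per microlitre); 1 ml = 1,000 microlitres.

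- As printed: 3,000 cells/ml ÷ 1,000 = 3 cells per microlitre.
- Against 3 x 10^3 per microlitre: 3,000 ÷ 3 = 1,000-fold lower.
- Against the section 5.1.2 limit: 4,000 ÷ 3 = 1,333-fold lower.

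If 4K were instead read per ml, the two limits would be on one scale (4,000 ÷ 3,000 = 1.33), but the outcome would then be a count of 4 per microlitre and equally unusable. On either reading the printed entry limit does not work. If the entry unit were per microlitre, the entry and outcome limits would still differ by 4,000 - 3,000 = 1,000 cells per microlitre. That may be deliberate, but the sponsor should say so.

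**2. GFR**

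Inputs: 45 mL/min per m2 (section 6.2); a body-surface reference of 1.73 m2, which is an assumption not found in the protocol, with 1.6 to 2.0 m2 as a range.

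Formula: limit per reference area = 45 x area.

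| Reference area (m2) | Literal limit (mL/min per that area) |
|---|---|
| 1.6 | 72.0 |
| 1.73 | 77.85 |
| 2.0 | 90.0 |

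On the 1.73 m2 reference, a patient with a reported value from 45 up to about 78 is eligible if staff compare the bare number with 45, and excluded if they apply the unit as printed. The literal reading is always the stricter one.

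**3. C-SSRS**

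| Item | Section 6.2 window | Appendix I recent window | Date field on the form |
|---|---|---|---|
| Ideation | 1 month | 1 month | not needed |
| Actual attempt | 1 month | 3 months | yes, most recent attempt |
| Interrupted attempt | 1 month | 3 months | none |
| Aborted attempt | 1 month | 3 months | none |
| Preparatory acts | 1 month | 3 months | none |

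For ideation the two agree. For an actual attempt the date settles the matter. For the other three behaviours, a negative recent answer shows that the criterion is not met. A positive one leaves open whether the event fell in the last month or in the two months before it. A free-text description might hold a date, but no field asks for one.

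**The case against.** The strongest reply is that section 6.2 has several layers and no patient group is left wholly uncovered.

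- **Immunosuppression.** A reader might infer that the faulty count is the protocol's only definition of immunosuppression. It is not. The count defines only the limb on current immunosuppression. The same bullet excludes active autoimmune disease and an immunocompromised state, of which chemotherapy is given as an example and not as the whole. The laboratory and investigator catch-alls add to this. This part of the reply stands. What it does not do is repair the number: apart from chemotherapy within three years, these backstops are largely judgement-based.
- **Confounding.** A reader might also infer that immunosuppressant use would be an unmeasured confounder of the cytokine mediation analysis (Hypothesis 3.1). The documents do not support this. Section 8.1 and the visit lists in section 10.1 record concomitant medication at screening and again at the infusion, clinical and final visits. Randomisation also balances such use in expectation. A new ban on these drugs would be a clinical choice, not the correction of an error.
- **GFR.** The missing 1.73 may be no more than a typing slip, and staff may simply compare the reported value with 45. That is plausible. A reader might infer that renal protection is lost, but the literal unit tightens the criterion.
- **C-SSRS.** An eligibility window narrower than the form's is a legitimate choice. An attempt 5 to 12 weeks before screening is not ignored either: section 5.1.2 calls for further investigation of any positive answer, and the investigator may exclude. This stands too. It remains that the criterion and the form use different windows, and that three of the four behaviour items carry no date.

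**Conclusion.** The point holds as two unit errors and one window conflict, of unequal weight.

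- The white-cell limit is the clear failure. As printed it is 3 cells per microlitre and excludes practically nobody, about 1,300-fold off the protocol's leukopenia limit if that is per microlitre.
- The GFR unit is wrong or incomplete. Its literal value of about 78 mL/min/1.73 m2 rests on a reference area that the protocol does not state. The consequence is wrongful exclusion or inconsistent application.
- The C-SSRS conflict is confined to behaviour, and in practice to interrupted attempts, aborted attempts and preparatory acts.

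It would go too far to say that all three exclusions fail to select the patients they name; that is fully true only of the white-cell count. The protocol gives no basis for estimating how many patients would be affected, and none is claimed here.

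**What to change.** Amend section 6.2 as follows.

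1. Correct the volume unit of the white-cell limit. The sponsor should confirm the intended limit, add a unit to the leukopenia limit in section 5.1.2, and state whether the entry and outcome limits are meant to differ.
2. Correct the GFR unit, with the sponsor confirming the intended limit and the reference area.
3. Reconcile the behaviour window in the C-SSRS exclusion with Appendix I. The sponsor should state which window applies. If it differs from the form's, the case report form needs a date for interrupted attempts, aborted attempts and preparatory acts.

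Which clinical limits and which window are right is for the sponsor to decide. The cost is amendment wording and, for item 3, possibly one added field. The blood count, metabolic panel and C-SSRS are already collected at screening (section 10.1.1).
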